### Criteria for discontinuing or modifying allocated interventions {11b}

At the discretion of the investigators, patients presenting with grade ≥ 2 RD, moist desquamation, or intense pain can be prescribed topical corticosteroids (methylprednisolone aceponate) until symptoms resolve. Any medication prescribed for local symptoms will be documented regarding dose, duration, and mode of application. Patients can withdraw informed consent at any point in time. If so, the reason(s) will be documented. Cross-over between arms is not planned.

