### Outcomes {12}

#### Clinician-reported outcome (CRO)

Patients will be evaluated during weekly on-treatment visits. Any additional visits requested by the participants will also be documented. RD severity of the irradiated breast will be assessed according to the National Cancer Institute’s Common Terminology Criteria for Adverse Events (CTCAE; version 5.0) [32]. Furthermore, hyperpigmentation, breast oedema, and desquamation (dry or moist) will be assessed and recorded. Upon radiation treatment completion, as well as 2 and 6 weeks later, acute toxicity will be reassessed. An experienced breast radiation oncologist, blinded to the allocation, will perform all clinical assessments. The topical corticosteroid prescription rate (to alleviate radiation dermatitis-related symptoms) will also be assessed in both arms.

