### Data management {19}

All data recorded during the trial will be pseudonymised, with patients being identifiable by a unique patient number. The identification list will be stored on a password-protected secure server. Data will be collected on trial-specific documentation sheets, signed and dated by the assessing radiation oncologist for every separate patient visit. All data will be transferred into a single database (electronic case report form). All trial documents will be securely stored for 10 years.

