### Adverse event reporting and harms {22}

Not applicable. In both initial trials, no adverse events were reported, in line with previous trials using NIPP for other skin disorders, confirming the complete absence of side effects.

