## Discussion

RD remains the most common acute side effect of breast irradiation and radiotherapy in general. Progress in the development of new prophylactic and therapeutic agents has been slow, leading to a considerable physical and psychological impact on numerous patients. While topical corticosteroids are effective in reducing RD-related symptoms, their widespread and prolonged use remains limited due to the associated side effect profile [42, 43]. Care should be taken especially if moist desquamation is present, as topical corticosteroids might delay wound healing or even promote infection.

Trials investigating new ways to prevent or treat RD often recruit heterogeneous patient collectives in terms of dose-fractionation regimens and treatment sites, with the majority lacking a uniform control group or adequate placebo control. Another issue is the subjectivity of physician-assessed RD gradings such as CTCAE or RTOG, the most common primary endpoints, with considerable inter- and intra-observer variability and significant discrepancies with the patient’s perspective [44]. To accurately investigate prevention and treatment strategies, there is a need for sufficiently powered randomised controlled trial, recruiting a homogeneous patient collective in terms of RD risk, with a robust design (including CRO, PRO, and objective assessments) and apt placebo control, as is the case in this proposed trial protocol.

If the trial results in breast cancer patients are promising, the beneficial effects and lack of side effects of NIPP could potentially be translated to other patients and treatment sites at-risk for developing RD, e.g. those receiving radiotherapy for head and neck or skin cancer, or even accidental radiation injuries of the skin [45]. Adjuvant breast irradiation is chosen as the primary setting to investigate the use of NIPP in this trial due to its high prevalence, homogeneous treatment sites and radiation dose-fractionation concepts.

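### Adverse event reporting is declared not applicable, so skin infection and events outside the listed outcomes have no systematic count by arm

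*Protocol article*

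**What the plan says.** All references are to the protocol article.

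- **Adverse event reporting and harms {22}** answers the item with "Not applicable. In both initial trials, no adverse events were reported, in line with previous trials using NIPP for other skin disorders", and adds that this confirms that side effects are entirely absent.
- **Interim analyses {21b}** uses the same record to dispense with an interim safety analysis and stopping rules.
- **Outcomes {12}, Clinician-reported outcome** has a blinded radiation oncologist grade radiation dermatitis by CTCAE v5.0 weekly, at the end of radiotherapy, and 2 and 6 weeks later. In addition, "hyperpigmentation, breast oedema, and desquamation (dry or moist) will be assessed and recorded". The corticosteroid prescription rate is assessed in both arms.
- **Outcomes {12}, Patient-reported outcome** adds pain, itching, burning and limitation in daily activities at the end of radiotherapy and at both follow-up visits.
- **Criteria for discontinuing or modifying allocated interventions {11b}** allows rescue treatment at the investigators' discretion: patients with grade 2 or worse dermatitis, "moist desquamation, or intense pain can be prescribed topical corticosteroids (methylprednisolone aceponate) until symptoms resolve".
- **Discussion** warns about such treatment: "Care should be taken especially if moist desquamation is present, as topical corticosteroids might delay wound healing or even promote infection". It also says that, if results are promising, "the beneficial effects and lack of side effects of NIPP could potentially be translated to other patients and treatment sites".

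**The concern.** A placebo-controlled trial with blinded assessment of individually randomised patients is a good place to learn whether an intervention has unwanted effects. The section Sequence generation {16a} says that NIPP probably diffused to the untreated half of the breast in the phase 2 trial, and that a separate control group is needed for that reason. By-arm safety information is therefore something this trial can supply, and the stated plan gives up part of it.

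The reason given covers only one of the treatments that patients receive. They also undergo radiotherapy and may be given a topical corticosteroid, which the Discussion itself links to delayed healing and infection when moist desquamation is present. Moist desquamation is one of the permitted reasons for prescribing it. Infection is nevertheless not a named outcome.

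At stake is what the trial can say about safety when it reports. If the plan is followed as written, a statement that NIPP lacks side effects would draw, for infection and unlisted events, on whatever happened to be found in visit and medication records.

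**Working it through.** No figure in the plan is in dispute and the documents give no event rate, so the check compares what is collected with what a statement about side effects needs.

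**Step 1. Is this an omission or a decision?** Section {22} gives an answer and a reason, and refers to no other document. The allowance that an article may leave detail to a full protocol or analysis plan therefore does not cover it.

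**Step 2. What is collected systematically?**

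| Item | Where | Collected in both arms? |
|---|---|---|
| Dermatitis grade (CTCAE v5.0) | {12}, clinician-reported | Yes |
| Hyperpigmentation, breast oedema, dry or moist desquamation | {12}, clinician-reported | Yes |
| Corticosteroid prescription rate | {12}, clinician-reported | Yes |
| Pain, itching, burning, limitation in daily activities | {12}, patient-reported | Yes |
| Skin colour | {12}, objective assessment | Yes |
| Skin infection of the irradiated breast | not named | No systematic item |
| Any other unlisted adverse event | {22}: not applicable | No systematic item |

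Statistical methods {20a} compares the clinician- and patient-reported outcomes and the colour readings between arms, so the first group of rows is served.

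**Step 3. Could the last two rows be recovered elsewhere?** Partly.

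- Medication log, {11b}: "Any medication prescribed for local symptoms will be documented regarding dose, duration, and mode of application". An infection treated with a local agent would leave a trace; one managed without medication would not. The stated fields are dose, duration and mode of application, not diagnosis.
- Extra visits, {12}: "Any additional visits requested by the participants will also be documented". This depends on the patient asking for a visit.
- Visit sheets, {19}: "Data will be collected on trial-specific documentation sheets, signed and dated by the assessing radiation oncologist for every separate patient visit". A sheet exists for every visit, but the article names no field for infection or other events.
- Relevant concomitant care {11d} says other acute toxicities of radiotherapy will be treated. It does not say they will be counted.
- The exit questionnaire at the last follow-up has several yes–no statements whose content is not given, so it cannot be relied on here.

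These sources could yield some events. None has every patient asked the same question at every visit, which a by-arm count with a known denominator requires.

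**Step 4. Does the stated reason support the decision?** It concerns NIPP alone. It says nothing about infection in patients who receive the rescue corticosteroid, in either arm, or about events in the placebo arm, against which NIPP would be judged.

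**The case against.** The strongest reply is that safety is far from ignored. The main expected local harms are graded by a blinded assessor on an adverse-event scale at repeated visits, and the clinician-reported section says acute toxicity is reassessed after treatment. The device is described as certified for this use {11a}. There are sealed envelopes for emergency unblinding {17b}, yearly on-site monitoring concerned with patients' rights and safety {23}, and planned investigator meetings {5d}. The Discussion's extrapolation is conditional and tentative. All of this stands, and it limits the point to infection and unlisted events. It does not close the gap, because none of these provisions produces a count by arm.

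A reader might also infer more than the documents support:

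- *That the trial collects no adverse event information.* The table above shows otherwise.
- *That an infection count by arm would reveal corticosteroid harm.* It would not. The corticosteroid is given after randomisation, at discretion, to patients with worse skin, and infection can arise without it. The count describes how often infection occurs in each arm, not its cause.
- *That zero events would bound the true rate.* With 70 analysed NIPP patients (Sample size {14}), the exact one-sided 95% limit would be 1 − 0.05^(1/70) = 4.2%. That applies only to a single event type assessed in every patient. Randomisation began on 15 February 2024 (Trial status), so an amendment cannot provide complete prospective assessment. Zero adverse events of any kind is also unrealistic in irradiated patients. The bound is therefore not claimed.
- *That the primary endpoint is biased.* Nothing here affects the dermatitis grade at the end of radiotherapy.

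**Conclusion.** The point holds in its limited form. Section {22} sets adverse event reporting aside on NIPP's earlier record, and the stated plan has no systematic by-arm count of skin infection or of adverse events outside the listed outcomes. The trial's own support for a wider claim of freedom from side effects would be weaker than its design allows.

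No numerical size is attached, because the documents give no rate for infection or other unlisted events. The conclusion rests on two readings: that the not-applicable entry means what it says, and that the visit sheets have no such field, since none is described. If the sheets already carry one, the change reduces to stating it in {22} and reporting it by arm. The point is a cheap improvement; efficacy results do not depend on it.

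**What to change.** Replace the not-applicable entry in Adverse event reporting and harms {22} with:

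> At each weekly, end-of-treatment, 2-week and 6-week visit the blinded assessor records any adverse event not already captured as an outcome (CTCAE v5.0), with new clinician-diagnosed skin infection of the irradiated breast as a named item. These are reported as number and percentage of patients by arm, with the number of patients prospectively assessed as the denominator.

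Patients seen before the amendment are reported separately, from existing records or as not assessed.

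**Cost.** No new visits, no new assessor, and no change to the primary endpoint or sample size. It needs a small addition to the visit sheet and one results table. It also needs an amendment by the route in {25}: review board approval, notice to the funder and trial staff, a registry update, and training if needed. The main drawback is incomplete coverage of patients already enrolled; the article does not say how many that is.

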### Frequency and plans for auditing trial conduct {23}

Yearly audits (on-site monitoring) will be carried out by a clinical research associate of the SZB, to ensure rights and safety of included patients and assess the reliability of trial results. Independent monitoring will be performed in accordance with a trial-specific risk-adapted manual, signed by all parties involved in conducting this trial, and involves the project management group and all involved trial personnel. Upon trial completion by the last patient, a close-out visit is scheduled.

### Plans for communicating important protocol amendments to relevant {25}

Amendments to the trial protocol can only be implemented upon approval by the responsible Institutional Review Board, through the principal investigator of the trial. Any changes to the protocol will be communicated with the funder and all trial personnel. A copy of the revised protocol will be added to the Investigator Site File and training will be provided if needed. The protocol in the clinical trial registry will be updated accordingly. In general, any deviations from the trial protocol will be documented using a breach report form.

### Dissemination plans {31a}

Results will be published in a peer-reviewed journal after database clearance and subsequent closure by a clinical research associate of the SZB.

## Discussion

RD remains the most common acute side effect of breast irradiation and radiotherapy in general. Progress in the development of new prophylactic and therapeutic agents has been slow, leading to a considerable physical and psychological impact on numerous patients. While topical corticosteroids are effective in reducing RD-related symptoms, their widespread and prolonged use remains limited due to the associated side effect profile [42, 43]. Care should be taken especially if moist desquamation is present, as topical corticosteroids might delay wound healing or even promote infection.

Trials investigating new ways to prevent or treat RD often recruit heterogeneous patient collectives in terms of dose-fractionation regimens and treatment sites, with the majority lacking a uniform control group or adequate placebo control. Another issue is the subjectivity of physician-assessed RD gradings such as CTCAE or RTOG, the most common primary endpoints, with considerable inter- and intra-observer variability and significant discrepancies with the patient’s perspective [44]. To accurately investigate prevention and treatment strategies, there is a need for sufficiently powered randomised controlled trial, recruiting a homogeneous patient collective in terms of RD risk, with a robust design (including CRO, PRO, and objective assessments) and apt placebo control, as is the case in this proposed trial protocol.

If the trial results in breast cancer patients are promising, the beneficial effects and lack of side effects of NIPP could potentially be translated to other patients and treatment sites at-risk for developing RD, e.g. those receiving radiotherapy for head and neck or skin cancer, or even accidental radiation injuries of the skin [45]. Adjuvant breast irradiation is chosen as the primary setting to investigate the use of NIPP in this trial due to its high prevalence, homogeneous treatment sites and radiation dose-fractionation concepts.

### Trial status

The current version of the protocol is version 1.0, dated on the 9th of November 2023. The trial has started enrolment in the first quarter of 2024 and the first patient was randomised on the 15th of February 2024. The trial is scheduled to take 36 months until completion (until the last quarter of 2026).

## Data Availability

Results will be published in a peer-reviewed journal upon clearance and closure of the database. Dissemination of individual patient data is not planned.

## Abbreviations

CIE: Commission Internationale de l’Éclairage
CRO: Clinician-reported outcome
CTCAE: Common Terminology Criteria for Adverse Events
CTV: Clinical target volume
DBD: Dielectric barrier discharges
DIBH: Deep inspiration breath-hold
eComp: Electronic tissue compensation
GDPR: General Data Protection Regulation
Gy: Grey
HER2: Human epidermal growth factor receptor 2
ICD: International Classification of Diseases
ICRU: International Commission on Radiation Units and Measurements
IMRT: Intensity-modulated radiotherapy
MV: Megavolt
NIPP: Non-invasive physical plasma
PRE: Patient-reported experience
PRO: Patient-reported outcome
PTV: Planning target volume
pT2: Primary tumour > 20 mm
RD: Radiation dermatitis
RISRAS: Radiation-Induced Skin Reaction Assessment Scale
RONS: Reactive oxygen and nitrogen species
RTOG: Radiation Therapy Oncology Group
SD: Standard deviation
SZB: Studienzentrale Bonn
